In addition, during the first educational session, the operation of the application will be explained so that the participant can become familiar and ask any questions, and notifications will also be set up to generate a daily reminder.

It is divided into three educational sessions so as not to saturate the participant with information, in this way it will be possible to strengthen the follow-up of the intervention and to resolve any doubts that may arise. These sessions will be conducted by the principal investigator.

The three phases described below do not require that the physiotherapist be always present during the operation. The participant can carry out the intervention autonomously at home, with prior training. The mobile application will record when the intervention has been carried out in order to facilitate follow-up and once a week, the principal investigator will follow up by telephone with the participant to make sure that the intervention is being carried out. . In addition, the application will include the personal email and telephone number of the researcher in order to facilitate contact at any time.

Phase 1. Laterality recognition:

The participant must observe images shown in the application, depending on the level of injury will observe images of upper or lower extremities, and differentiate with the shortest possible time if it is the right or left side of the body.

- Session intensity: 10 minutes.
- Frequency: Two sessions a day.
- Phase duration: 5 days a week for three weeks.
- Phase progression:

Day 1-5: Images in neutral positions in the different planes.

Day 6-10: Images in different positions in the different planes.

Day 11-15: Interaction with objects and functional activities.

The accuracy of the accuracy of each activity and the time used to identify each image will be recorded through the application.

Phase 2. Motor imagery:

This phase will be done through the mobile application. During the activity, images will appear, depending on the level of amputation, and the participant will have to imagine that he / she places his / her limb in the same position as the one in the image and returns it to the initial position, without perform voluntary contraction, will only perform a mental simulation, whether it is the side of the amputation or not.

- Session intensity: 10 minutes.
- Frequency: Two sessions a day.
- Phase duration: 5 days a week for three weeks.
- Phase progression (Same progression as phase 1)

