Day 1-5: Images in neutral positions in the different planes.

Day 6-10: Images in different positions in the different planes.

Day 11-15: Interaction with objects and functional activities.

Each activity will also be recorded through the app. Before the start of the motor imaging phase, during the educational session, the project researcher will assess the person’s ability to imagine through the kinesthetic and visual imagination questionnaire (KVIQ) 12. It is a 10-item quiz where the physiotherapist teaches different movements and the person has to rate their ability to imagine them in the first person. In the event of a impairment of imagination, the person will be taught different strategies to do so. One of them will be before the intervention to show him/her videos and images of the affected limb in order to pre-activate the areas through the observation of the action. Another strategy is to make your imagination run wild first or try to find a factor or situation that helps you to imagine it. On the other hand, pain can occur during the imagination phase. If it appears, the person can be instructed to first imagine the movement with the healthy limb. If the pain is still triggered, we can ask you to imagine the movement in the third person. These strategies will be modified throughout the intervention to allow the person to realize the mental imagination in the first person.

Phase 3. Mirror therapy:

This phase is done with a mirror box, the mobile application is no longer used. The mirror box will be provided by the research team and once the intervention is completed, it must be returned. The participant should place the mirror in the sagittal plane between the two extremities, so that he observes the healthy end in the mirror (reflection) and the amputated end is behind the mirror. The limb behind the mirror should initially have no voluntary contraction or intentional contraction. The participant will later be asked if he or she intends to contract the stump. The size of the mirror will vary depending on the level of injury and the joints involved. If pain appears during the intervention, external factors can be sought to help tolerate the intervention (music, images ...). However, if the pain persists, it should be stopped at that time.

- Session intensity: 20 minutes
- Frequency: Once a day.
- Phase duration: 5 days a week for three weeks
- Phase progression:

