The data obtained as study variables will be coded at the end of the collection, processed and analyzed by the members of the research group.

The population to be used as a sample in the analysis will include all participants who meet all the inclusion criteria, do not have any exclusion criteria and have given their consent to participate in the study. If a participant leaves before completing the study, he / she will not be replaced by another participant.

In the case of participants who have not completed the study due to dropout, have not fully completed treatment, or have even changed treatment, any data that may have been collected will be analyzed for intent to treat. The minimum number of sessions to be considered for the results will be 80%.

The program to be used for statistical analysis will be the SPSS5 program. A confidence level of 95%, and / or a statistical significance p <0.05 will be considered.

If a deviation from the intended method is considered necessary during the data analysis process, the reasons for any change will be fully documented.

To describe the sample, a descriptive statistic will be performed analyzing the mean, standard deviation, minimum, maximum and percentages of the sociodemographic variables. In addition, it will be possible to look at the average of those included and excluded in order to justify the excluded people. In this way it will be possible to describe the sample and observe the homogeneity between groups.

Next, a univariate and bivariate statistical analysis will be performed. First of all, it will be assessed whether or not the study follows a normal distribution in each of the variables. This analysis will determine whether to use parametric or non-parametric tests in the analysis of results based on the "p" value.

Equality of variance will then be analyzed through the Levenne test and finally the results will be analyzed. There will be a pre- and post-intervention analysis between groups and intragroups with a three-month follow-up. We can also analyze possible correlations between variables.

Qualitative analysis:

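### The protocol promises intent to treat but also requires 80% of sessions for a participant to count; applied to the main analysis, the 80% rule would thin the GraMI arm only

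*Protocol*

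**What the plan says.** All of the analysis wording is in the Protocol, Statistical analysis, under Quantitative analysis.

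- **Population.** The analysis sample "will include all participants who meet all the inclusion criteria, do not have any exclusion criteria and have given their consent". No adherence condition is attached.
- **Incomplete treatment.** For participants who dropped out, or who "have not fully completed treatment, or have even changed treatment", the protocol says that "any data that may have been collected will be analyzed for intent to treat".
- **Session minimum.** The next sentence reads: "The minimum number of sessions to be considered for the results will be 80" (per cent). It gives no analysis set, arm or denominator, and does not say whether it concerns a primary or a supportive analysis.

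The session schedule is under Step 2: RCT. Phases 1 and 2 each carry "Frequency: Two sessions a day" of 10 minutes and "Phase duration: 5 days a week for three weeks". Phase 3, mirror therapy, is one 20-minute session a day over the same 15 days. Of phase 3 the protocol says: "This phase is done with a mirror box, the mobile application is no longer used". The investigator telephones intervention participants weekly throughout. Controls continue the conventional treatment they already receive and keep an activity diary; no number of sessions is prescribed for them.

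**The concern.** The two adjacent sentences give different answers for the same person. A GraMI participant who did 50% of sessions has not fully completed treatment, so is analysed by intent to treat. The same participant is below 80%, so does not count for the results. As written, the analyst must choose between the rules, and could do so after seeing the data.

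The choice matters because the threshold has practical meaning in one arm only. People who keep up a self-administered home programme may differ in prognosis from those who do not. Comparing selected adherers with all controls gives up the protection of randomisation. The trial is also small (25 per group, with no dropout allowance stated), so removing people from one arm costs power too.

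**Working it through.** **1. The planned sample size.** Inputs from the sample size section: effect size 0.81, 25 per group. The printed error rates (alpha 0.5, beta 0.8) are read here as alpha 0.05 two-sided and power 0.80. A two-sample t-test then needs 24.92, so 25 per group, which reproduces the stated 50. Power with 25 versus 25 is 80.1%. This is the reference when nobody is removed.

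**2. Session count, from Step 2: RCT.**

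| Phase | Sessions | Minutes |
| --- | --- | --- |
| 1 Laterality recognition | 2 × 5 × 3 = 30 | 300 |
| 2 Motor imagery | 2 × 5 × 3 = 30 | 300 |
| 3 Mirror therapy | 1 × 5 × 3 = 15 | 300 |
| Total | 75 | 900 |

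The threshold is 0.80 × 75 = 60 sessions, which equals the 30 + 30 app sessions. Counted by days, phases 1 and 2 are 30/45 = 66.7%; by minutes, 600/900 = 66.7%. If educational sessions count as well, completing phases 1 and 2 gives 62/78 = 79.5% or 63/79 = 79.7%, depending on whether three or four such sessions are counted. So the unstated denominator decides whether phases 1 and 2 alone are enough.

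**3. Bias if the rule is applied to the main comparison.** Assumptions, none from the protocol: no true effect, outcome SD 1, adherence normally distributed with correlation ρ to a better outcome, a share k of the GraMI arm kept (the best adherers), and all 25 controls kept. The spurious difference is ρ × φ(z)/k, where z is the normal quantile at 1 − k and φ the normal density. For k = 0.9, 0.8, 0.7 and 0.6, φ(z) is 0.1755, 0.2800, 0.3477 and 0.3863. For example, with ρ = 0.5 and k = 0.6: 0.5 × 0.3863/0.6 = 0.322.

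Each cell gives the spurious difference in SD, then the two-sided type I error from simulation (40,000 replicates, t-test at 0.05):

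| Kept | ρ = 0.1 | ρ = 0.3 | ρ = 0.5 |
| --- | --- | --- | --- |
| 90% | 0.02; 5.0% | 0.06; 5.4% | 0.10; 6.4% |
| 80% | 0.03; 5.3% | 0.10; 6.4% | 0.17; 8.9% |
| 70% | 0.05; 5.2% | 0.15; 7.5% | 0.25; 12.0% |
| 60% | 0.06; 5.3% | 0.19; 8.7% | 0.32; 16.2% |

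**4. Power at d = 0.81 from the loss of numbers alone.**

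| GraMI arm removed | Arms | Power |
| --- | --- | --- |
| 0% | 25 vs 25 | 80.1% |
| 10% | 22 vs 25 | 77.4% |
| 20% | 20 vs 25 | 75.2% |
| 30% | 18 vs 25 | 72.5% |
| 40% | 15 vs 25 | 67.6% |

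**The case against.** The best defence is that the 80% sentence is a loosely worded adherence or per-protocol definition meant to sit beside intent to treat. The population statement carries no adherence condition, and details of a per-protocol set are often left to a statistical analysis plan, which is not at hand. It would therefore be too strong to say that the protocol fixes an adherence-filtered main analysis. What stands against the defence is that the sentence speaks of the results without qualification, follows directly on the intent-to-treat sentence, and names no supportive set. The conflict is in the protocol's own text.

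The rule is also not limited to one arm in words. That it would act on one arm follows from the schedule, since no session count is prescribed for controls.

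Three stronger readings are tempting and are not supported:

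- **That the threshold lets participants skip mirror therapy.** This needs all 60 app sessions, then none of the 15 mirror sessions, and a count by exercise sessions. It fails by days, by minutes, or if educational sessions count. It shows that the denominator is undefined, no more.
- **That phase 3 is unmonitored.** The app is not used, but the weekly call continues and is meant to check that the intervention is being done. What the protocol does not state is a session record for that phase.
- **That the result would certainly be biased, and in favour of GraMI.** The protocol has no data on how adherence relates to outcome. That direction is plausible, but it is an assumption.

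**Conclusion.** The concern holds as a conflict between two stated rules about who enters the main comparison. If the 80% rule governs that comparison, it selects within the GraMI arm only and can bias the result. The bias is negligible when few are removed and adherence is weakly related to outcome (0.02 SD, type I error about 5%). It is material when 40% are removed and the correlation is 0.5 (0.32 SD, about 16%). Retention and correlation are both assumed, and the true values may lie anywhere in or beyond that range. The loss of power, from 80% to between 77% and 68% for 10% to 40% removed, depends only on the assumed share removed and the planned effect size. If the sentence was meant as a supportive definition, none of this affects the main result, but the protocol has to say so.

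**What to change.** In Statistical analysis, replace the session-minimum sentence with two statements:

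1. The primary analysis includes all randomised participants with data, in the group to which they were assigned, whatever number of sessions they did.
2. The 80% threshold defines only a named supportive analysis, per-protocol or complier-average, with the denominator stated (for example, 75 exercise sessions, educational sessions not counted).

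For that supportive analysis, record the number of phase 3 sessions at the existing weekly call. A threshold within each phase (24 of 30, 24 of 30, 12 of 15) would ensure that adherence covers all three techniques, but it is optional.

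The cost is a few sentences and one extra item at the weekly call. The all-randomised estimate may be somewhat smaller than the estimate in adherers.

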**Specific objectives:**

- Design a mobile application to be able to carry out the intervention and determine its usability.

- Analyze the effectiveness of the GraMI protocol in the quality of life, functionality and psychological aspects of amputated patients.

- Know the experience of the person with PLP after amputation and identify the satisfaction obtained with the intervention

1. **DESIGN**:

A RCT with a mixed methodology will be carried out, with two parallel arms and blindly simple, following the recommendations of *the Consolidate Standards of Reporting Trials - CONSORT*(11), and a phenomenological study through semi-structured interviews, following the recommendations of *the Standards for Reporting Qualitative Research*(7) which will be carried out once the intervention is over. The clinical trial was registered at ClinicalTrials.gorv (registration number: NCT05083611).

1. **SETTING:**

It will be done at the community level individually. The intervention will be carried out by the participant himself / herself and will be supervised with a follow-up by the principal researcher. The semi-structured interviews will be individual and carried out in person or by video call once the intervention is over.

1. **SIMPLE SIZE**

The sample was calculated using the G * Power program, taking into account an alpha error of 0.5, a beta error of 0.8, and an effect size of 0.81(9). In order to calculate the sample we rely on existing scientific evidence. A study11 has been selected to assess phantom limb pain using the McGill Pain Short-Form Questionnaire, and the intervention used is based on mirror neurons. The total number of participants would be 50, with 25 in each group.

1. **INCLUSION AND EXCLUSION CRITERIA:**

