The researcher conducting the interview will be an external person who has not performed the intervention or randomization, so as not to influence the questions and answers. This person has theoretical sensitivity about PLP and mirror therapy and this will make it easier to delve deeper into the topics during the interviews and better understand the experience. Subsequently, two members of the research group will perform the transcripts and analysis of the results. The aim of this triangulation is to achieve the highest possible objectivity in the results. The interviews will be recorded in voice and video format in order to be able to make a transcript as optimal as possible and will help not to lose the facial and body expressions of the participant. Only the research group and the researcher who conducted the interviews will have access to the recorded material. Each participant will have previously signed the consent to the image and voice rights. Once the study is complete, the recordings will be deleted. Once the transcripts have been completed, they will be sent to each participant to corroborate the information. This process will also be performed after the analysis of the results. You can see the consent form and the interview template in the appendices.

1. **VARIABLES:**

The assessments will be carried out by two people outside the intervention and the phenomenological study. These people will be two physiotherapists with clinical experience in the field of neurorehabilitation and / or pain, trained in research methods, calibrated with each other in order to minimize bias and will be blinded by the assignment of the groups. An initial assessment, a post-intervention assessment (9 weeks) and a follow-up assessment (12 weeks post-intervention) will be performed. The assessments will be carried out in the homes of the participants, in person and will last approximately 25-30 minutes.

The variables to be studied are differentiated between sociodemographic variables, amputation characteristics, independent variables and dependent variables. The first assessment will be the one that will last longer as all the variables will be collected, but the second and third assessment will last approximately 30 minutes as only the dependent variables will be collected.

- **Socio-demographic variables**; gender, age, marital status, height, level of education, level of physical activity, pathological and traumatic history, drugs administered and dose.

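### The main between-group comparison names no adjustment for baseline pain, and a normality p-value picks the test; a prespecified ANCOVA would be more precise and would fix the effect measure in advance

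*Protocol*

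**What the plan says.** Protocol, Statistical analysis, Quantitative analysis: after describing the sample, "a univariate and bivariate statistical analysis will be performed". Normality is assessed for each variable, and "This analysis will determine whether to use parametric or non-parametric tests in the analysis of results", on the basis of a p-value. Levene's test for equal variances comes next. The comparison itself gets one sentence, which announces a before-and-after analysis both between and within the arms, with a three-month follow-up. No covariate, model or single effect estimate is named. The threshold is given as "A confidence level of 95%, and / or a statistical significance p <0.05 will be considered".

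Protocol, Variables: "An initial assessment, a post-intervention assessment (9 weeks) and a follow-up assessment (12 weeks post-intervention) will be performed". Every variable is collected at the first assessment, so each participant has a baseline SF-MPQ score.

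Protocol, sample-size section: the calculation is described as "taking into account an alpha error of 0.5, a beta error of 0.8, and an effect size of 0.81(9", and "The total number of participants would be 50, with 25 in each group".

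**The concern.** There are two separate issues.

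**Precision.** Baseline pain is usually correlated with later pain. With 25 per arm, the standardised baseline difference between arms has standard error sqrt(2/25) = 0.28, so a chance imbalance of more than 0.3 SD in either direction would arise in about 29% of such trials. A comparison of post scores carries r times that imbalance into the estimate. A comparison of change scores subtracts the whole baseline value, which over-corrects when r is below 1. ANCOVA estimates the right amount of correction from the data. In a trial of 50 with 80% planned power, the difference can matter.

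**Prespecification.** A t-test concerns a difference in means; a rank test does not. If a p-value computed on the outcome data decides between them, the primary test and the effect measure are unknown until the data are in. They may also differ between the two follow-up visits, or between pain and the secondary scales. The report might then have no single effect estimate with a confidence interval that runs through the trial.

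**Working it through.** **Inputs.** Effect size d = 0.81 and 25 per arm (Protocol, sample-size section). Two-sided alpha 0.05 and power 0.80: the section prints an alpha of 0.5 and "a beta error of 0.8", read here as 0.05 and power 0.80 because the first agrees with the analysis threshold and together they reproduce the stated sample size. Assumptions not in the Protocol: r between 0.3 and 0.7; d standardised by the post-score SD; equal SDs at baseline and follow-up.

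**Step 1: reproduce the plan's figure.** Two-sample t-test, noncentral t, with noncentrality d·sqrt(n/2) = 0.81 × sqrt(12.5) = 2.86 on 48 df. This gives power 0.801 at 25 per arm, and 25 is the smallest n that reaches 0.80. The stated total of 50 is therefore an unadjusted, two-sided, two-sample calculation. A one-sided test would need only 40.

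**Step 2: effective effect size under each comparison.**
- Post scores: d = 0.81, whatever r is.
- Change scores: the SD of change is SD·sqrt(2(1−r)), so effective d = 0.81/sqrt(2(1−r)).
- ANCOVA: the residual SD is SD·sqrt(1−r²), so effective d = 0.81/sqrt(1−r²), on 47 df.

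| r | Change: effective d | ANCOVA: effective d | Power, post | Power, change | Power, ANCOVA |
|---|---|---|---|---|---|
| 0.3 | 0.81/1.183 = 0.68 | 0.81/0.954 = 0.85 | 0.801 | 0.660 | 0.837 |
| 0.5 | 0.81/1.000 = 0.81 | 0.81/0.866 = 0.94 | 0.801 | 0.801 | 0.899 |
| 0.6 | 0.81/0.894 = 0.91 | 0.81/0.800 = 1.01 | 0.801 | 0.880 | 0.939 |
| 0.7 | 0.81/0.775 = 1.05 | 0.81/0.714 = 1.13 | 0.801 | 0.952 | 0.975 |

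**Step 3: variance ratios.** ANCOVA against post scores: 1−r² = 0.91, 0.75, 0.64 and 0.51. ANCOVA against change scores: (1−r²)/(2(1−r)) = (1+r)/2 = 0.65, 0.75, 0.80 and 0.85. Both ratios are below 1 for any r between 0 and 1, so the ranking does not depend on which SD was used to standardise 0.81; only the power figures do. At r = 0.5, 25 per arm with ANCOVA is worth about 25/0.75 = 33 per arm on post scores.

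**Step 4: does the normality rule itself do harm?** A simulation (25 per arm, 3,000 runs per setting, r = 0.3, 0.5 and 0.7) let a Shapiro-Wilk test choose between the t-test and the Mann-Whitney test on post scores.
- Type I error of the two-stage procedure was 0.045 to 0.058 over normal and skewed data, so there was no material inflation.
- With normal data, its power was 0.80 to 0.81, against 0.82, 0.90 and 0.97 for ANCOVA. The plain t-test did as well as the two-stage procedure, so the gap is due to the missing covariate.
- With skewed (log-normal) data and a pure shift, the two-stage procedure had power 0.94 to 0.95, against 0.84, 0.87 and 0.95 for plain ANCOVA. There the rank test it mostly selects matched or beat an ANCOVA on untransformed scores.

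**The case against.** The strongest reply is that covariates and the exact model are commonly left to a statistical analysis plan, which may exist, and that the unadjusted plan is valid and reaches its stated power. This stands in part. Randomisation keeps the unadjusted estimate unbiased, and 50 participants give 0.801. But the Protocol does more than stay silent: it fixes a univariate and bivariate framework and a data-driven choice of test. A later plan with a baseline-adjusted primary model would have to depart from that text.

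Four stronger readings are tempting, and the Protocol does not support them.
- **That baseline pain is never used in the group comparison.** The sentence on a before-and-after analysis between arms can be read as a comparison of change scores, which does use the baseline. The gain from ANCOVA must therefore be shown against both comparators. At r = 0.6 and 0.7 it is much smaller against change scores; at r = 0.3 it is larger.
- **That the normality rule wastes precision or inflates type I error.** The simulation shows neither, and with skewed data the rank test can do better than plain ANCOVA.
- **That Levene's test acts as a second gate.** The text only says that equality of variances will be examined; no decision hangs on the result.
- **That intention to treat turns into a complete-case analysis.** This would follow only from a specific test that the Protocol never names. An ANCOVA at a single visit would equally leave out anyone without that visit.

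**Conclusion.** The point holds as an improvement that should be made, not as an error that invalidates the plan. On either reading of the comparison, ANCOVA is more precise. Against post scores, power rises from 0.80 to between 0.84 and 0.975 as r goes from 0.3 to 0.7. Against change scores, it rises from 0.66 to 0.84 at r = 0.3 and from 0.95 to 0.975 at r = 0.7. These figures rest on an assumed r, on 0.81 being standardised by the post-score SD, on similar SDs at baseline and follow-up, and on roughly normal residuals. If the scores are clearly skewed, the advantage of plain ANCOVA over a rank test may shrink or reverse.

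The normality rule is a fault of its own kind: it leaves the primary test and effect measure unfixed until the data are seen. A reader might infer that the sample size is wrong. It is not, for the unadjusted test on which it is based.

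**What to change.** In the Quantitative analysis text, before outcome data are seen:
- State the main analysis as a linear model of SF-MPQ on arm with baseline SF-MPQ as covariate, in all randomised participants with follow-up data. This can be ANCOVA, or a mixed model over both follow-up visits with arm, visit, arm-by-visit and baseline. The mixed model also keeps participants who have only one of the two follow-up values.
- Report the adjusted mean difference between arms with its 95% confidence interval.
- Check the residuals; use robust or bootstrap standard errors if they are skewed, and give a rank-based test as a sensitivity analysis.
- Remove the rule by which a normality p-value chooses the primary test.
- Use the same approach for EQ-5D-5L, FIM and the Beck inventory.

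The cost is one degree of freedom (48 to 47) and a change of wording. No further data, visits or participants are needed.
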